#### Between group analyses

Ordinal data from UCLA scores and Kellgren-Lawrence grades will be compared at baseline and at 3 months (UCLA score only) between the control and KAM-R group using Mann–Whitney U tests (α = 0.05). KOOS subsection scores, PASE scores, KAMs, KAM impulse, varus thrust, adiposity, footwear comfort, and adherence will be compared at baseline between the KAM-R and control group using a MANOVA test (α = 0.05) with independent-samples t-tests for post-hoc analysis. Changes over 3 months will also be assessed between groups using a MANOVA (α = 0.05) with independent-samples t-tests for post-hoc analysis. All tests will be two-tailed, except in the case of KAMs and KAM impulse, where one-tailed tests will be used. The reason for this is that KAM reduction is strictly controlled in this study and so a reduction in KAMs and KAM impulse is the only possible outcome. It should be noted that all between group comparisons are exploratory analyses, as we may not be powered to detect any significant differences between groups.

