#### Physical activity

Two physical activity scales will be used in this study. The first is the UCLA physical activity scale. This scale provides a global measure of activity, and is commonly used in osteoarthritis populations undergoing arthroplasty [38]. The second is the Physical Activity Scale for the Elderly (PASE). PASE will be used to evaluate the type and duration of recreational and occupational physical activity of the previous week [39]. This scale was originally developed and validated for individuals over the age of 55 years, which is appropriate for the majority of the knee OA population. The purpose of the physical activity scales are to identify whether physical activity levels generally increased, decreased or remained constant during the study for experimental and control participants. The tests will be administered at baseline, and at 1 month, 2 months and 3 months follow-up.

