### Secondary outcome measures

Secondary outcome measures include the remaining four KOOS subsection scores (symptoms, function (daily living), function (sport & recreation activities), quality of life; 0–100 points each), PASE (0-400+ points) and UCLA (0–10 points) physical activity scores, peak KAM (Nm), KAM impulse (Nms), varus thrust (mm), adiposity (%), footwear comfort (0–100 mm) and the general intervention adherence survey. In addition, we will use Kellgren-Lawrence grade (grade 1–3) in secondary analyses.

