#### Within group analyses

All data will be analyzed on an intention to treat basis. Changes from baseline to 3 months will be assessed within groups for ordinal data (UCLA score) using Wilcoxon Signed Rank test (α = 0.05). KOOS subsection scores and PASE scores will be compared between baseline and at 3 months using paired-samples t-tests (α = 0.05). KAMs, KAM impulse, varus thrust, and footwear comfort will be compared between the neutral shoe and assigned wedged insole condition at baseline for the KAM-R group using paired-samples t-tests (α = 0.05). All tests will be two-tailed, except in the case of KAMs and KAM impulse, where one-tailed tests will be used. The reason for this is that KAM reduction is strictly controlled in this study and so KAM and KAM impulse reductions are the only possible outcome.

A multivariable linear regression (α = 0.05) will also be conducted on the KAM-R group to evaluate whether KAM reduction, KAM impulse, varus thrust and footwear comfort can predict change in pain over 3 months. Covariates tested in these four models will include adiposity and Kellgren-Lawrence grade.

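### The between-arm comparison of UCLA activity leaves out each participant's baseline score, which costs precision in an exploratory secondary analysis

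*Protocol article*

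**What the plan says.** All of this is in the protocol article.

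- **Between group analyses.** UCLA scores are "compared at baseline and at 3 months (UCLA score only) between the control and KAM-R group" by Mann–Whitney U tests. The next sentence lists the MANOVA variables. PASE and the KOOS subscales are in that list and UCLA is not. Then: "Changes over 3 months will also be assessed between groups using a MANOVA (α = 0.05) with independent-samples t-tests for post-hoc analysis".
- **Within group analyses.** "Changes from baseline to 3 months will be assessed within groups for ordinal data (UCLA score) using Wilcoxon Signed Rank test (α = 0.05".
- **Physical activity.** The two activity scales, UCLA and PASE, share one purpose: to "identify whether physical activity levels generally increased, decreased or remained constant during the study for experimental and control participants". They also share one schedule: "The tests will be administered at baseline, and at 1 month, 2 months and 3 months follow-up".
- **Secondary outcome measures.** UCLA is listed among the secondary outcomes.
- **Status of between-arm tests.** The Between group analyses section closes by noting that "all between group comparisons are exploratory analyses, as we may not be powered to detect any significant differences between groups".

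**The concern.** The baseline UCLA score enters the between-arm analysis only as a test of its own. It is neither subtracted from the 3-month score nor used as a covariate. Testing baseline and 3 months separately does not link the two: the baseline test may reveal a chance imbalance, but it corrects nothing in the 3-month test.

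Two things follow. First, the 3-month comparison carries all the between-person variation in activity that the baseline score could have removed. Second, with about 20 participants per arm, a chance difference at baseline carries over in part to 3 months and is read there as an arm difference. PASE, which has the same purpose and schedule, does get a between-arm comparison of change, so the two scales are handled differently.

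At stake is how well an exploratory analysis can show whether activity differed between arms after 3 months. No primary conclusion depends on it.

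**Working it through.** **Inputs from the protocol**
- 20 per group, two-sided α = 0.05 (Sample size calculation; two-tailed for UCLA under Between group analyses).
- No UCLA standard deviation, effect or correlation is given.

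**The protocol's own figure.** The 20 per group was set for KOOS pain (13.4 points, SD 15, 80% power). It reproduces: 2 × (15 × (1.960 + 0.842) / 13.4)² = 19.67, rounded up to 20. It is used here only as the number per arm.

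**Assumptions.** A between-arm difference d = 0.5 SD at 3 months, equal SDs at both times, and a baseline-to-3-month correlation ρ of 0.3, 0.5 or 0.7.

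**Formula.** Power ≈ Φ( d√(n/2) / f − 1.960 ), where f is the residual SD relative to the 3-month SD:
- 3-month score alone: f = 1
- baseline-adjusted: f = √(1 − ρ²)
- raw change score: f = √(2(1 − ρ))

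With d = 0.5 and n = 20, d√(n/2) = 0.5 × √10 = 1.581.

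*3-month score alone:* Φ(1.581 − 1.960) = Φ(−0.379) = 35%, whatever ρ is.

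| ρ | Adjusted: f | Adjusted: power | Change score: f | Change score: power |
|---|---|---|---|---|
| 0.3 | 0.954 | 38% | 1.183 | 27% |
| 0.5 | 0.866 | 45% | 1.000 | 35% |
| 0.7 | 0.714 | 60% | 0.775 | 53% |

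Adjustment reduces the number needed to 1 − ρ² of that for the 3-month score alone: 91%, 75% and 51%. Put the other way, 20 per arm with adjustment is worth about 22, 27 or 39 per arm without it (20/0.91, 20/0.75, 20/0.51).

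The change score beats the 3-month score only when 2(1 − ρ) < 1, that is ρ > 0.5. At ρ = 0.3 it is weaker, 27% against 35%.

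**Carry-over of chance imbalance.** At 20 per arm the standard error of the baseline mean difference is √(2/20) = 0.32 SD. Under a linear model a fraction ρ of a baseline difference is expected to persist. An imbalance of that size would therefore shift the 3-month difference by about 0.09, 0.16 or 0.22 SD at ρ = 0.3, 0.5 or 0.7.

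**Check on an ordinal scale.** Integer scores from 1 to 10 were simulated (assumed mean 5, SD 2, shift 1 point, 20 per arm, 3,000 trials per setting). The rank ANCOVA contained arm and baseline rank only; sex was not included.

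| ρ | Mann–Whitney, 3 months | Rank ANCOVA | Mann–Whitney, change |
|---|---|---|---|
| 0.3 | 32.2% | 34.5% | 23.4% |
| 0.5 | 31.2% | 38.2% | 31.0% |
| 0.7 | 31.5% | 50.5% | 46.7% |

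With no shift, all three methods rejected in 4.5% to 5.5% of trials at these correlations. The planned test keeps its error rate. The gains are somewhat smaller than in the formula but have the same direction and order.

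**The case against.** **The planned test is valid.** Under randomisation the 3-month Mann–Whitney test is a proper test of no arm difference, and the simulation confirms its error rate. This stands: the fault is lost efficiency, not bias.

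**Change is already tested.** A reader might infer that the plan fails to answer its own question about change in activity. The documents do not support that. The stated purpose concerns the direction of change among experimental and control participants, and the within-group Wilcoxon test addresses it. What is absent is a between-arm comparison of UCLA that takes account of baseline. Two within-arm p-values do not supply it, since one can be significant and the other not without the arms differing.

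**Low power is declared and UCLA is secondary.** Both are true and limit the importance of the point. They do not argue against using data already in hand.

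**The risk of false reassurance.** A reader might also infer that a missed UCLA difference would hide the main rival explanation for a pain result. The protocol gives activity no such role; the rival explanation it discusses is placebo. Activity is measured after randomisation and could be a result of pain relief. PASE change is compared between arms in any case. And even after adjustment, power at ρ = 0.5 is 45% for 0.5 SD, so a null result would still not reassure.

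**The MANOVA sentence on changes might include UCLA.** It names no variables, but it follows a list that omits UCLA, and UCLA is treated as ordinal with rank tests in both analysis sections. If UCLA were meant, the result would be t-tests on raw change, which conflicts with that treatment and is still not baseline-adjusted.

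**Such detail may sit in a fuller document.** The article does not leave this open: it names the test and the time points.

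**Conclusion.** The point holds as a small, avoidable loss of precision. No between-arm analysis of UCLA uses the baseline score, and part of any chance baseline difference remains in the 3-month comparison. At 20 per arm and a 0.5 SD difference, power is about 35% as planned, against 38%, 45% or 60% with adjustment at correlations of 0.3, 0.5 or 0.7.

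The effect size and the correlations are assumptions, because the protocol gives neither for UCLA. At a correlation of 0.3 the gain is only 3 percentage points. The direction is clearer than the size: in large-sample terms any non-zero correlation favours adjustment.

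The contrast with PASE might suggest treating UCLA the same way, on change. The figures do not support that below a correlation of 0.5. The change is desirable rather than necessary, and neither the primary outcome nor the sample size is affected.

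**What to change.** Under Between group analyses, replace the 3-month Mann–Whitney test for UCLA with a rank-based ANCOVA, or a proportional-odds model, of the 3-month UCLA score on arm and baseline UCLA. Include sex as a covariate, because allocation uses separate block sequences for males and females. Keep the exploratory label. Do not substitute a raw change score. The within-group Wilcoxon test can stay as it is.

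The cost is one sentence of analysis text. Baseline UCLA and sex are already available, so no visit, questionnaire or participant is added.

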### Randomization

Following the baseline laboratory and survey testing, participants will be randomized into one of two study arms: (1) a KAM-reduction experimental group (KAM-R), or (2) a waitlist control group. In the KAM-R group, participants will be given either a medial or lateral wedge insole (whichever insole reduces KAMs more for each individual participant) to put inside their own shoe and use for 3 months. In the waitlist control group, participants will be asked to continue using their own shoes for a period of 3 months, and following this will be provided with access to a wedged insole (whichever reduces KAMs more based on baseline data collection).

Participants will be randomized using a multi-block-randomization procedure into either the KAM-R or waitlist control group. Specifically, a separate block sequence will be used for males and females to ensure an even sex distribution across groups. A block size of 6 will be used for each, and the sequence will be determined from a random number generator.

The one exception to this block randomization procedure is that if neither wedged insole produces a KAM reduction, the participant will be excluded from the main study altogether. This scenario will not be common, as most people do experience a large change in KAMs with one of the two wedged insole types, but this strategy will ensure that all participants in the KAM-R and waitlist control groups are all biomechanically suitable for a wedged insole intervention. Thus, neither group will contain biomechanical non-responders to wedged insoles.

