### Sample size calculation

Sample size calculations were performed based on our primary outcome variable, the KOOS pain score, with a desired power of 80% and a significance level of 0.05 using the statistical software Stata version 11.2. Given the early stage of research concerning the effects and interactions of load reduction, and different OA subtypes on treatment outcome, we chose to only conduct sample size calculations on a repeated measures basis for within group comparisons. Based on the results of this trial, sample sizes may be expanded to increase statistical power in order to make comparisons between the control and KAM-R group.

The minimum perceptible clinical improvement and minimum detectible change in KOOS score has been reported to be about 13.4 points [33, 41]. Using a baseline KOOS pain score of 57.3 points [42] and a standard deviation of 15 points [41], to detect a minimal clinically important improvement of 13.4 points within each group, 20 participants are required in each group, or 40 total participants. To account for a potential dropout rate of 15%, we will recruit a minimum of 46 participants.

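### Randomisation is blocked by sex, but the between-group tests of 3-month outcomes leave sex out; this costs precision only if sex predicts the outcome (minor)

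*Protocol article*

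**What the plan says.** The Randomization section of the protocol article states that "a separate block sequence will be used for males and females to ensure an even sex distribution across groups", and "A block size of 6 will be used for each". The Between group analyses section names the tests: "Changes over 3 months will also be assessed between groups using a MANOVA (α = 0.05) with independent-samples t-tests for post-hoc analysis". UCLA score, treated as ordinal, is compared at 3 months "between the control and KAM-R group using Mann–Whitney U tests (α = 0.05"). Neither sentence contains a sex term or a stratified form of the test. The baseline comparisons in the same section take the same form, a MANOVA "with independent-samples t-tests for post-hoc analysis".

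The only covariates named in the statistical sections belong to a regression confined to the KAM-R arm: "Covariates tested in these four models will include adiposity and Kellgren-Lawrence grade". Sex is not among them. The Between group analyses section closes by saying that "all between group comparisons are exploratory analyses, as we may not be powered to detect any significant differences between groups".

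**The concern.** Balancing the arms on sex by design removes sex as a source of chance difference between them. An independent-samples t-test does not know this. It pools all variation within each arm, including any variation between men and women, into its error term. If sex is related to the outcome, the test reports a larger standard error than the design delivers. Intervals are then too wide, and the test rejects less often than its nominal 5%.

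The hypothesis at the end of the Background is a between-group one: greater improvement in pain and function than in the control group. These tests are the only ones that address it, and the plan already concedes that they may lack power. The Sample size calculation section also says that numbers may later be expanded to support between-group comparisons, so the precision seen here could feed a later decision.

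**Working it through.** **Inputs from the article.** SD 15 points; difference 13.4 points; 20 evaluable per arm; 46 recruited for 15% dropout (Sample size calculation, "with a desired power of 80% and a significance level of 0.05"). Blocks of 6 within sex (Randomization). Two-tailed test for KOOS pain (Between group analyses).

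**Assumed, not in the article.** A male–female difference in the outcome of 0 to 1.0 total SD (0 to 15 points); 50% women, with 60% as a sensitivity case; 1:1 allocation within blocks.

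**Step 1: reproduce the stated size.** The two-sample formula gives n per arm = 2 × 15² × (1.960 + 0.842)² / 13.4² = 450 × 7.85 / 179.56 = 19.7, so 20. Power at 20 per arm is 80.6% by the normal approximation and 78.6% by the noncentral t. Then 40 × 1.15 = 46. The article describes this calculation as within-group. That is a separate matter: this check needs only the SD, the difference and the arm size.

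**Step 2: expected size of the mismatch.** If a proportion p are women and the sexes differ by d total SDs, sex explains R² = p(1 − p)d² of the variance. The unadjusted standard error is 15 × √(2/20) = 4.74. Under exact balance on sex the true standard error is 4.74 × √(1 − R²). With p = 0.5:

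- d = 0.2: R² = 0.01, true SE 4.72
- d = 0.5: R² = 0.0625, true SE 4.59
- d = 0.8: R² = 0.16, true SE 4.35
- d = 1.0: R² = 0.25, true SE 4.11

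Balance is not quite exact, because 20 per sex is three full blocks of 6 and 2 left over. The simulated true standard errors are therefore slightly larger at the higher values of d.

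**Step 3: simulation.** Permuted blocks of 6 within sex, 40 participants, half women, total SD held at 15, 40,000 trials per setting. Each trial was analysed by a t-test without sex and by a linear model with sex.

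| Sex difference | True SE, no sex term | Mean reported SE, no sex term | Type I error, without / with sex | Power at 13.4, without / with sex |
|---|---|---|---|---|
| 0 | 4.77 | 4.71 | 5.1% / 5.0% | 78.1% / 78.0% |
| 0.2 SD (3 points) | 4.72 | 4.72 | 5.0% / 5.1% | 78.9% / 79.1% |
| 0.5 SD (7.5 points) | 4.61 | 4.72 | 4.5% / 5.1% | 79.3% / 81.0% |
| 0.8 SD (12 points) | 4.39 | 4.74 | 3.5% / 5.2% | 80.0% / 84.9% |
| 1.0 SD (15 points) | 4.16 | 4.75 | 2.4% / 4.9% | 81.1% / 88.8% |

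The overstatement of the standard error is 4.72/4.61 = 1.02, 4.74/4.39 = 1.08 and 4.75/4.16 = 1.14 in the last three rows.

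**Step 4: sensitivity.** With 46 recruited, 15% random loss and half women, type I error is 4.4% against 5.0% at 0.5 SD and 2.8% against 4.9% at 1.0 SD. Power there is 77.9% against 79.6%, and 79.4% against 87.5%. Sixty per cent women gives the same pattern. For a true effect of 10 points with 40 participants, the power forgone is 2.7, 7.2 and 12.2 points at 0.5, 0.8 and 1.0 SD.

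The check covers one continuous outcome at a time. The MANOVA and the Mann–Whitney test were not simulated.

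**The case against.** The strongest reply is that the loss may be nil. Nothing in the article shows that sex predicts change in KOOS pain. Because the continuous outcomes are compared as changes, a stable difference in level between men and women cancels; only a sex difference in change matters. The larger losses need a difference of 12 to 15 points, about the size of the 13.4-point improvement the trial regards as clinically important. All of this stands, and it makes the point conditional. It applies less to UCLA, which is compared as a 3-month score, so a sex difference in activity level stays in that comparison.

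A reader might infer that the planned tests are conservative regardless, or that power falls to 70–75%. The article supports neither. Power that low appears only if the sex difference is added on top of an SD of 15, raising the total to √(15² + 10²/4) = 15.8 for 10 points or √(15² + 15²/4) = 16.8 for 15 points. The article does not say that its SD is within sex. With total SD held at 15, unadjusted power stays at 78.1 to 81.1%. Adjustment offers a possible gain; its absence does not pull power below what was planned. Nor is the stratification wasted: its stated aim is an even sex distribution, and blocking delivers that whatever the analysis.

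It is also fair that the tests are exploratory, that the sample size is not said to rest on them, that the estimate is unbiased and false positives are not inflated, and that the baseline comparisons have no treatment-effect power to lose. These points limit the severity.

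The last reply, that an unseen analysis plan may add the stratum, carries less weight. A MANOVA could take a sex factor, but an independent-samples t-test and a plain Mann–Whitney test cannot, and those are the procedures the article names.

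**Conclusion.** The mismatch between the sex-blocked randomisation and the tests of 3-month outcomes is in the text. Its consequence depends on a sex effect that the article does not give. Under the working assumptions (single-outcome t-test, total SD 15, 20 per arm) it ranges from nothing measurable at 0 to 0.2 SD, through about 2 power points at 0.5 SD, to 5 to 8 power points at 0.8 to 1.0 SD, always in the conservative direction. Carrying the direction over to the MANOVA and the rank test is reasoning, not calculation. Severity is minor: a near-free gain in precision for exploratory comparisons that nonetheless address the trial's stated hypothesis.

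**What to change.** In Between group analyses, state that the between-arm models of change in KOOS, PASE and the other continuous outcomes include sex, the randomisation stratum, as a fixed term. The follow-up t-tests become linear models with arm and sex. For UCLA at 3 months, replace the Mann–Whitney test with its sex-stratified (van Elteren) form. The baseline comparisons need no change on this account.

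The cost is a sentence or two and one degree of freedom (error degrees of freedom 37 instead of 38 with 40 participants). No new data are needed, since sex is already recorded for allocation. If sex turns out not to be prognostic, the continuous outcomes lose at most about 0.2 power points. The corresponding cost for the stratified rank test was not calculated.

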#### Biomechanics

Eight Motion Analysis cameras (Motion Analysis Corp., Santa Rosa, CA) sampling at 240 Hz will record the 3D trajectories of retroreflective markers placed over the participants most symptomatic limb as they walk along a 20 m runway. A force platform (Kistler AG, Winterthur, Switzerland) will collect ground reaction force data at a frequency of 2400 Hz as the participant walks along the runway. This will be done for 5 successful trials in each of 3 footwear conditions for each participant: (1) participant’s own shoe (baseline condition), (2) participant’s own shoe with the lateral wedge insole, and (3) participant’s own shoe with the medial wedge insole. A successful trial is defined as one where the participant lands with their most symptomatic limb near the center of the force platform, does not touch the force platform with their other limb, and maintains a gait speed of 1.3 ± 0.07 m/s as measured by two photocells.

Kinetic and kinematic data will be filtered using 4^th^ order Butterworth low-pass filters with cut-off frequencies of 50 Hz and 12 Hz, respectively. KAMs during stance will be calculated using an inverse dynamics approach, and the peak KAM (first peak) will be identified for each trial [4, 19]. The average KAM across trials for each footwear condition will then be calculated and represented as a percent change from the baseline condition value. The KAM impulse (integral of KAMs with respect to time) and Varus thrust (maximum mediolateral displacement of knee joint center from touchdown) [24] and the KAM impulse (integral of KAMs with respect to time) [25] will also be calculated as these variables have also been shown to be related to knee OA [6, 24]. At the baseline visit, biomechanical testing and DXA scans will be performed and survey information will be collected. After determining the peak KAMs for all three conditions, the percent change in KAM will be determined for the medial and lateral wedge conditions.

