#### Adherence

At baseline, participants will be asked to refrain from utilizing any alternate therapies during the study period (aside from anti-inflammatory or acetaminophen medication), and asked to utilize the prescribed footwear condition as frequently as possible during the day. While not an exclusion criteria of this study, participants will be asked to try and always use the insole in the same shoe tested at baseline. We will conduct a survey at 1 month, 2 months and 3 months follow-up to evaluate participant adherence to the intervention, which will include recall of the number of hours per day using the assigned insole over the past week, recall of the number of times in the past week a different shoe from baseline was used with the insole, and recall of the number of times alternate allowable therapies were used, such as targeted exercise for OA or anti-inflammatory and acetaminophen medications. Use of therapies that are considered as exclusion criteria (i.e. viscosupplementation, knee braces, narcotic pain medication), will also be recorded.

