#### Comfort

Some studies have suggested that footwear comfort may be an important variable in determining the effectiveness of a footwear intervention on pain management [40]. Therefore, we will administer a paper-based 100 mm visual analog scale with the terms “extremely comfortable” and “extremely uncomfortable” as anchors at 100 mm and 0 mm, respectively. The tests will be administered on paper at baseline.

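### The baseline MANOVA includes adherence, which has no baseline value; the change MANOVA names no variables; and KOOS pain is compared between arms only by a post-hoc t-test

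*Protocol article*

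**What the plan says.** The Between group analyses section of the protocol article sets two multivariate tests at α = 0.05, each followed by independent-samples t-tests as post-hoc analysis.

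- Baseline: "KOOS subsection scores, PASE scores, KAMs, KAM impulse, varus thrust, adiposity, footwear comfort, and adherence will be compared at baseline" by MANOVA. With five KOOS subscales, that is 12 variables.
- Follow-up: "Changes over 3 months will also be assessed between groups using a MANOVA". This sentence has no variable list of its own.
- Sidedness, for the same paragraph: "All tests will be two-tailed, except in the case of KAMs and KAM impulse, where one-tailed tests will be used".
- The section closes by calling all between-group comparisons exploratory and possibly underpowered.

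The schedule is given elsewhere in the article.

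- Adherence: "We will conduct a survey at 1 month, 2 months and 3 months follow-up to evaluate participant adherence to the intervention".
- Biomechanics and DXA: "At the baseline visit, biomechanical testing and DXA scans will be performed and survey information will be collected". The Body composition section likewise places DXA at baseline.
- Comfort: "The tests will be administered on paper at baseline".
- KOOS and PASE: baseline and 1, 2 and 3 months.

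KOOS pain is the only primary outcome (Primary outcome measures). The hypothesis that closes the Background is that the insole group improves more than the control group. Randomisation uses separate block sequences for men and women (Randomization).

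**The concern.** Three things do not fit together.

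1. A MANOVA needs a value of every component for each participant. Adherence has no baseline value for anyone, and its main item, hours of use of the assigned insole, has no counterpart in a waitlist arm without an insole.
2. The change MANOVA follows directly on the 12-variable list, and the one-tailed rule after it still treats KAM and KAM impulse as outcomes. An analyst could reasonably carry the list over and find that several variables have no 3-month value. An analyst who does not carry it over has to choose the variables.
3. The primary outcome has no between-arm test of its own. If the t-test is done only after a significant MANOVA, a real difference in pain can go undeclared because of noise in secondary scores.

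At stake is the only comparison in the trial that randomisation protects. The Sample size calculation section also says that the results may lead to a larger sample for comparing the arms. That decision needs an estimate and interval for pain, which an omnibus test does not give.

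**Working it through.** **Step 1. Variables against schedule**

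| Variable | Baseline value | 3-month change |
|---|---|---|
| Five KOOS scores, PASE | yes | yes |
| KAM, KAM impulse, varus thrust | yes | no |
| Adiposity (DXA) | yes | no |
| Footwear comfort | yes | no, by the Comfort section |
| Adherence | no | no (follow-up only) |

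The baseline MANOVA has no complete case while adherence is in it. The change MANOVA has six usable variables (5 + 1). For comfort, the Abstract lists the scale among the surveys and says that survey tests are repeated at 3 months. The Comfort section gives baseline only, and the two should be reconciled. The other four baseline-only variables are unaffected by this.

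**Step 2. One-tailed rule**

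With two arms and n per arm, MANOVA is Hotelling's T² = (n/2)·D′S⁻¹D, where D is the vector of mean differences and S the pooled covariance matrix. This is a quadratic form and has no direction. A one-tailed rule can apply only to the follow-up t-tests, and no 3-month KAM is scheduled.

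**Step 3. The plan's own figure**

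Inputs from Sample size calculation: "with a desired power of 80% and a significance level of 0.05"; a target of 13.4 points, "to detect a minimal clinically important improvement of 13.4 points within each group"; SD 15; 20 per group.

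- Two-sample formula: n = 2·[(1.960 + 0.842)·15/13.4]² = 19.67, rounded up to 20 per group. This matches the plan.
- Paired formula with 15 as the SD of change: half of that, 9.8, rounded up to 10.
- Dropout: 40 × 1.15 = 46, which matches.

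The 20 per group therefore reproduces from the independent-groups formula, although the text describes a within-group basis.

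**Step 4. KOOS pain tested directly**

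Assumptions not in the document: the within-group target of 13.4 is reused as the between-arm difference, and 15 is the SD of change. The standardised difference is 13.4/15 = 0.893. A two-sided t-test (noncentral t) has power 78.6% at 20 per arm and 84.2% at 23 per arm.

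**Step 5. KOOS pain gated by a six-variable MANOVA**

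The gate is F = T²·(2n − p − 1)/[p(2n − 2)] on p and 2n − p − 1 degrees of freedom. With p = 6 and n = 20 these are 6 and 33. Joint power is the probability that both the MANOVA and the pain t-test reach p < 0.05, by simulation with 8,000 replicates per setting. All six variables share one common correlation. Cells show joint power, with the points lost against the t-test alone in brackets.

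| Effect pattern | ρ = 0 | ρ = 0.3 | ρ = 0.5 | ρ = 0.7 |
|---|---|---|---|---|
| Pain only | 43% (36) | 51% (27) | 63% (15) | 75% (3) |
| Half effect on the other five | 70% (8) | 47% (32) | 44% (35) | 47% (31) |
| Equal effect on all six | 79% (0) | 73% (6) | 63% (15) | 54% (24) |

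At 23 per arm the range is 0 to 34 points.

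**Step 6. Sensitivity to PASE**

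Now take 20 per arm, the full effect on all five KOOS scores, none on PASE, and inter-subscale correlation 0.5 or 0.7.

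- PASE uncorrelated with KOOS: joint power about 61% and 53% against 79%, a loss of about 18 and 26 points.
- PASE–KOOS correlation 0.3: a loss of about 12 and 21 points.
- PASE correlated with KOOS as strongly as the subscales are with each other: a loss of about 1 to 3 points.

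**Step 7. Direction**

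Passing two tests is never more likely than passing one of them, so the gate can lower power for pain or leave it unchanged, but cannot raise it.

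**The case against.** The strongest reply is that the article labels every between-group comparison exploratory, sizes the trial for within-group change, and gives the KOOS scores direct paired t-tests within each arm. No between-group power was promised, so none is lost. That stands as far as it goes. It does not make the baseline test runnable, and limited power is a reason not to add a further hurdle.

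A reader might infer that the randomised comparison of pain cannot be estimated at all. The documents do not support that. The change MANOVA names no variables and runs on KOOS and PASE changes, and adherence at baseline has no bearing on it. It fails only if the baseline list is carried over, which the one-tailed KAM sentence suggests but does not state.

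A reader might also take 18 to 26 points as the cost. That is one scenario and depends on PASE being uncorrelated with KOOS. The article gives no correlations, no effect pattern and no between-arm difference.

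The gate itself is inferred. The text calls the t-tests post-hoc but does not say that they depend on a significant MANOVA. If they do not, the MANOVA does nothing for the pain comparison, and the plan should say so.

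Handling of missing components may be left to a fuller plan and is not part of this point.

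**Conclusion.** The point holds in a limited form and should be fixed.

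- Certain from the text: the baseline MANOVA is unrunnable as written; the change MANOVA has no stated variable list; the one-tailed rule has no meaning for an omnibus statistic; and KOOS pain has no between-arm test of its own.
- Conditional: the change MANOVA is unrunnable only if it inherits the baseline list, and the power loss arises only if post-hoc means conditional on the MANOVA.
- Size: about 0 to 36 points of power with six variables at 20 per arm. This rests on an assumed 13.4-point between-arm difference and an SD of change of 15, over the correlations and effect patterns shown. The direction is certain and the amount is not.

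The planned change-score t-test also subtracts baseline pain without adjusting for it, and ignores the sex stratification used at randomisation, although both are already collected.

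**What to change.** - Replace the change MANOVA with a direct, ungated between-arm comparison of KOOS pain change at 3 months, by ANCOVA or a mixed model adjusted for baseline KOOS pain and sex stratum. Report the estimate and confidence interval. It can keep its exploratory label.
- Analyse the other four KOOS scores and PASE with the same model, as secondary estimates with intervals.
- Remove adherence from the baseline comparison and describe it after baseline.
- Treat KAM, KAM impulse, varus thrust, adiposity and comfort as baseline-only variables. Reconcile the Abstract with the Comfort section on when comfort is measured.
- Drop the one-tailed rule from the between-group change analysis, where no KAM change exists.

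The cost is one reworded paragraph and simpler code, with no change to data collection. The omnibus test's loose multiplicity control over the secondary scores is lost. With a single primary outcome, and the rest reported as estimates, that is a small price.
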